## Abstract

**Background:**

The lack of health care coverage, low education, low motivation, and inconvenience remain barriers to participating in fall prevention programs, especially among low-income older adults. Low-income status also contributes to negative aging self-perceptions and is associated with a high perceived barrier to care. Existing fall prevention intervention technologies do not enable participants and practitioners to interact and collaborate, even with technologies that bring viable strategies to maintain independence, prevent disability, and increase access to quality care. Research is also limited on the use of technology to enhance motivation and help individuals align their perception with physiological fall risk. We developed a novel, 8-week Physio-Feedback Exercise Program (PEER), which includes (1) technology-based physio-feedback using a real-time portable innovative technology—the BTrackS Balance Tracking System, which is reliable and affordable, allows for home testing, and provides feedback and tracks balance progression; (2) cognitive reframing using the fall risk appraisal matrix; and (3) peer-led exercises focusing on balance, strength training, and incorporating exercises into daily activities.

**Objective:**

This study consists of 3 aims. Aim 1 is to examine the effects of the technology-based PEER intervention on fall risk, dynamic balance, and accelerometer-based physical activity (PA). Aim 2 is to examine the effects of the PEER intervention on fall risk appraisal shifting and negative self-perceptions of aging. Aim 3 is to explore participants’ experiences with the PEER intervention and potential barriers to accessing and adopting the technology-based PEER intervention to inform future research.

**Methods:**

This is an intention-to-treat, single-blinded, parallel, 2-arm clustered randomized controlled trial study. We will collect data from 340 low-income older adults at baseline (T1) and measure outcomes after program completion (T2) and follow-up at 3 months (T3) and 6 months (T4). Participants will be enrolled if they meet all the following inclusion criteria: aged ≥60 years, cognitively intact, and able to stand without assistance. Exclusion criteria were as follows: a medical condition precluding exercise or PA, currently receiving treatment from a rehabilitation facility, plan to move within 1 year, hospitalized >3 times in the past 12 months, and does not speak English or Spanish.

**Results:**

As of August 2023, the enrollment of participants is ongoing.

**Conclusions:**

This study addresses the public health problem by optimizing a customized, technology-driven approach that can operate in low-resource environments with unlimited users to prevent falls and reduce health disparities in low-income older adults. The PEER is a novel intervention that combines concepts of physio-feedback, cognitive reframing, and peer-led exercise by motivating a shift in self-estimation of fall risk to align with physiological fall risk to improve balance, PA, and negative aging self-perception.

**Trial Registration:**

ClinicalTrials.gov NCT05778604; https://www.clinicaltrials.gov/ct2/show/study/NCT05778604

**International Registered Report Identifier (IRRID):**

DERR1-10.2196/51899

## Introduction

### Background

In 2020, there were 37.2 million people living in poverty in the United States, approximately 3.3 million more than in 2019 [1]. Every 19 minutes, an American individual dies from a fall, and every 11 seconds, an older individual is treated in an emergency department for a fall [2]. Falls and fear of falling (FOF) are significantly higher in racially diverse low-income older adults than in the general older population [3-5]. There is an association between poverty, fall injury, and mortality, resulting in health disparities [6,7]. Falls cause 95% of hip fractures, 40% of admissions to facility-based care, and 40% of fall victims to lose mobility and independence [8]. In 2018, the direct costs of fatal falls were >US $754 million, and nonfatal falls were US $50 billion, but only US $9 billion was paid by Medicaid [9]. As the number of low-income older adults increases sharply and inequalities continue to grow, this is now a widely recognized problem that requires urgent and significant action [10]. The lack of health care coverage, low education, low motivation, and inconvenience remain barriers to participating in fall prevention programs [11,12]. Low-income status contributes to negative aging self-perceptions [13] and is associated with a high perceived barrier to care [14]. A higher level of concern over falling and FOF were more prevalent in low-income older adults and functional independence in daily activities [12]. Low-income status is independently associated with FOF, which induces activity restriction [15] and functional decline [16]. People who live in low-income communities are less likely to engage in physical activity (PA) [17-19]. The lack of PA is related to falls and poor quality of life [20,21].

Addressing maladaptive fall risk appraisal (FRA) can be challenging owing to self-report bias and cognitive deficit. We developed an *FRA matrix*, a graphical grid categorizing perception (levels of FOF) and body function (level of balance) into four groups: (1) rational FRA (low FOF and normal balance), (2) incongruent FRA (low FOF despite poor balance), (3) irrational FRA (high FOF despite normal balance), and (4) congruent FRA (high FOF and poor balance) [22,23]. On the basis of our previous works [24-26] and other studies [27], approximately 64% to 79% of older adults had maladaptive FRA. Older adults in maladaptive FRA groups were 2 to 3 times more likely to fall than those in adaptive FRA [24,25]. Those with irrational FRA serve as a barrier, creating a high FOF that inhibits low-income older adults from staying physically active. High FOF restricts mobility and daily activities and increases fall risk [28], with chronic FOF predicting an increased risk of functional decline [16]. Individuals with FOF overestimated their gait performance and showed deficits in motor imagery of gait [29]. They may not exhibit increased FOF and subsequently fall if they accurately appraise their physical abilities [27]. Evidence, including our data, indicates that an intervention program must help older adults reframe FRA and maintain PA [27,30]. We found that the FRA matrix is associated with moderate to vigorous PA (MVPA), Centers for Disease Control and Prevention (CDC) fall risk score, self-reported strength and flexibility, difficulty walking several city blocks, and left-hand average handgrip strength [31].

Older adults with FOF overestimated their gait performance and showed deficits in motor imagery of gait [29]. Older adults may exhibit less FOF and subsequently fall if they accurately appraise their physical abilities [27]. In addition, maladaptive FRA can result in activity withdrawal, decline in physical and cognitive abilities, and increased social isolation [23]. Therefore, adaptive FRA is a key component of activity participation and maintenance of self-reliance [32]. Several types of interventions focus on reducing FOF [33-41]; however, some degree of FOF can increase conscious awareness and reduce fall risk by encouraging individuals to avoid exposure to unnecessary risks [42]. Low-income older adults with better-perceived physical health may experience less FOF [43].

In addition, existing fall prevention intervention technologies do not enable participants and practitioners to interact and collaborate [44] even with technologies that bring viable strategies to maintain independence, prevent disability, and increase access to quality care. Acceptability, privacy issues, technology costs, implementation costs, and barriers have rarely been addressed [44]. Research is also limited on the use of technology to enhance motivation and help individuals align their perception with physiological fall risk [45]. Offering additional advantages, technology-based exercise interventions have good adherence and may provide a sustainable method of promoting PA and preventing falls [45,46].

We developed a novel, 8-week Physio-Feedback Exercise Program (PEER) [32], which includes (1) technology-based physio-feedback using a real-time portable innovative technology—the BTrackS Balance Tracking System (BBS), which is reliable [47,48] and affordable, allows for home testing, provides feedback, and tracks balance progression; (2) cognitive reframing [49] using the FRA matrix; and (3) peer-led exercises [50] focusing on balance, strength training, and incorporating exercises into daily activities. Our pilot study supports the feasibility and acceptability of using BBS technology in low-income communities to screen individuals with maladaptive FRA. It also supports using the results to tailor interventions to improve PA and reduce falls [31,51,52]. The findings highlight reducing sedentary time to help shift from irrational to rational groups and increasing MVPA time to help shift from congruent and irrational to rational FRA groups. We found a significant difference in sedentary time between the rational and irrational groups (*P*=.04). This indicates that if a person exhibits high FOF despite their normal balance (irrational), they tend to be more sedentary compared with people with low FOF and normal balance (rational). Importantly, we showed that the FRA matrix and 4-group quadrant design (irrational, incongruent, congruent, and rational) allows stratified analysis, which provides a more efficient overall fall risk assessment, which has rarely been reported in the literature.

### Aims and Hypotheses

Aim 1 is to examine the effects of the technology-based PEER intervention on fall risk, dynamic balance, and accelerometer-based PA.

The hypotheses are as follows:

*H 1.1:* The PEER group will reduce the fall risk compared with the control group.*H 1.2:* The PEER group will improve the dynamic balance compared with the control group.*H 1.3:* The PEER group will improve accelerometer-based PA compared with the control group.

Aim 2 is to examine the effects of the PEER intervention on FRA shifting and negative self-perceptions of aging.

The hypotheses are as follows:

*H 2.1:* The PEER group will have a more adaptive shifting compared with the control group.*H 2.2:* The PEER group will have a more positive shift in their perceptions of aging compared with the control group.

Aim 3 is to explore participants’ experiences with the PEER intervention and potential barriers to access and adoption of the technology-based PEER intervention to inform future research. A purposive sample of 30 participants from the PEER group will participate in semistructured one-on-one interviews to explore their perceptions of barriers to access and adoption of technology and intervention.

## Methods

### Study Design

This is an intention-to-treat, single-blind, parallel, 2-arm clustered randomized controlled trial study. We will collect data at baseline (T1) and measure outcomes after program completion (T2) and follow-up at 3 months (T3) and 6 months (T4) to test our hypotheses. We include a retention period of 6 months to determine whether fall risk, dynamic balance, PA, altered maladaptive FRA (FRA shifting), and negative self-perceptions of aging are maintained without ongoing intervention. This study is registered on ClinicalTrials.gov (NCT05778604).

### Settings

The intervention will be offered in low-income, independent living communities, units, and apartments in Orlando, Florida. Florida has a large aging population with drastically different income levels and degrees of socioeconomic status [53]. The diversity of potential participants is also high, as Florida’s population is approximately 17% African American, 3% Asian, 26% Hispanic or Latinx, and 54% non-Hispanic White [54].

### Study Participants

A sample of 340 participants will be enrolled if they meet all the following inclusion criteria:(1) aged ≥60 years, (2) cognitively intact based on Mini-Mental State Examination score ≥24 [55], and (3) able to stand without assistance. Exclusion criteria were as follows: (1) a medical condition precluding exercise and PA, such as feeling pressure when performing PA; (2) currently receiving treatment from a rehabilitation facility; (3) plan to move within 1 year; (4) hospitalized >3 times in the past 12 months; and (5) does not speak English or Spanish.

### Power Analysis and Sample Size

The sample size estimate was based on the primary outcomes of fall risk (CDC fall risk score) and PA (normalized MVPA) for aim 1 and the secondary outcome of FRA shifting (BBS score) for aim 2. The difference in the normalized mean MVPA between the PEER group (mean 3.67, SD 2.54) and the control group (mean 5.38, SD 2.68) and the difference in the fall risk score between the PEER group (mean 2.72, SD=3.23) and the control group (mean 2.21, SD=2.06) are considered markers of PA and fall risk, respectively. Considering a clinically relevant normalized difference in MVPA of 1.7 (SD 2.60) and a fall risk score difference of 0.50 (SD 2.56), the medium effect size Cohen *d*=0.25, intraclass correlation (ICC) of 0.8, and a significance level of are used for the calculation of the sample size. A sample size of 120 participants per arm is needed to reach 80% statistical power to detect the difference between the PEER and control groups on repeated measures of normalized MVPA. A sample size of 120 participants per arm is needed to reach 80% statistical power to detect the difference between the PEER and control groups on repeated measures of normalized MVPA.

In addition, the sample size was also based on the following: (1) at least 3 sites per arm; (2) an initial hypothesis that at least 10% (34/340) of the irrational, incongruent, and congruent FRA would shift to rational FRA after PEER completion; (3) an approximate study adherence rate of 80% [56], and (4) an estimated study dropout rate of approximately 40% (136/340) over time. Therefore, the sample size was increased from 120 to 170 per arm, resulting in a total of 340 participants. On the basis of our pilot study [26], we estimate that approximately 60% (204/340) of the low-income older adults will meet all inclusion and exclusion criteria and will be interested in participating in this study. We estimate that a minimum of 567 low-income older adults will be screened to identify 340 low-income older adults for enrollment, and approximately 240 low-income older adults (120 per arm) are needed to complete the study. Given the sample size of 120 per arm, a significance level of *P*=.05, and 80% power, considering a clinically relevant BBS mean score difference of 8 (SD 12), the effect size Cohen *d*=0.36 can be achieved to compare the intervention effect based on secondary outcomes.

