#### Secondary Outcome Measures

##### FRA Shifting

*FRA shifting* consists of (1) maladaptive shifting, which is moving from the rational quadrant into any other quadrant, and (2) adaptive shifting, which is moving from irrational, incongruent, or congruent into the rational quadrant [77]. We use the FRA matrix, a graphical grid categorizing levels of FOF (mind) and levels of balance (body) into four quadrants [22,23]: (1) *rational:* low FOF (short Falls Efficacy Scale-International [FES-I] ≤10) and normal balance (BBS ≤30), (2) *incongruent:* low FOF (short FES-I≤10) despite poor balance (BBS>30), (3) *irrational:* high FOF (short FES-I>10) despite normal balance (BBS≤30), and (4) *congruent:* high FOF (short FES-I>10) and poor balance (BBS>30).

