*H 2.1*: The PEER group will have a more adaptive shifting compared with the control group.*H 2.2*: The PEER group will have a more positive shift in their perceptions of aging compared with the control group.

To test hypothesis *2.1* (FRA shifting), the 4 FRA quadrants will be determined by grid coordinates based on 2 continuous level measures (BBS and short FES-I scores). We will classify shifting into 2 types: maladaptive and adaptive shifting. Adaptive shifting is moving from irrational, incongruent, or congruent to rational. The outcome is a percentage of low-income older adults with baseline (T1) in irrational, incongruent, or congruent quadrants who end up in the rational quadrant after program completion (T2). Maladaptive shifting is a movement from rational to any other quadrant, and the percentage of low-income older adults will be calculated. After program completion (T2), the baseline FRA categories (T1) may remain the same or shift to a different FRA category. We will form a 4×4 contingency table for the 4 FRA categories at each follow-up time point (T3 and T4) to summarize the shifts. The standard 4×4 table analysis will be performed to examine the FRA shifting, either using a chi-square test or exact test, depending on the actual counts observed in the 4×4 table. The BBS and short FES-I scores will be collected in 4 planned visit time points (T1, T2, T3, and T3). We will use the Generalized Linear Mixed Model (GLMM) to analyze these 2 end points for assessing the difference between the PEER intervention and control arms on the shift of FRA categories [109]. Our longitudinal data on the PEER effects of different types of shifting on low-income older adults will contain repeated binary measures of the shifting status over time. The binomial GLMM with the logic link will allow us to assess the difference between the 2 arms in FRA shifting, and the associated LRT [101] will be used to test hypothesis *2.1* if a significant adaptive shifting is detected in the PEER group compared with the control group. The GLMM can address the group heterogeneity by specifying the corresponding covariance structure in random effect terms.

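### The 80% power stated for FRA shifting is for a difference in mean BBS score, not for the binary test of H 2.1

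*Protocol article*

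**What the plan says.** All references are to the protocol article.

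**Power Analysis and Sample Size.** The sizing rests on the aim 1 primary outcomes and on "the secondary outcome of FRA shifting (BBS score) for aim 2". The only power statement for aim 2 begins "Given the sample size of 120 per arm", continues with "a significance level of *P*=.05, and 80% power" and "considering a clinically relevant BBS mean score difference of 8 (SD 12"), and ends that "the effect size Cohen *d*=0.36 can be achieved to compare the intervention effect based on secondary outcomes". The same section lists, as a further basis for the sample size, that "at least 10% (34/340) of the irrational, incongruent, and congruent FRA would shift to rational FRA after PEER completion". No control rate, test or power goes with that 10%.

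**FRA Shifting (secondary outcome measures).** Adaptive shifting is "moving from irrational, incongruent, or congruent into the rational quadrant". The rational quadrant requires short FES-I ≤10 and BBS ≤30 together.

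**Data Analysis, H 2.1.** The outcome is the percentage, among those in one of the other three quadrants at T1, "who end up in the rational quadrant after program completion (T2"). The named test is the likelihood ratio test of a binomial GLMM on repeated binary shifting status. The same paragraph also says that the BBS and short FES-I scores will be analysed by GLMM.

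**The concern.** The sizing section treats FRA shifting and the BBS score as the same thing. They differ in three respects.

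- **Scale.** The power is for a difference in means. The test is on a binary outcome.
- **Construct.** Irrational participants already have BBS ≤30, so they can shift only through short FES-I. Congruent participants must improve on both scales. Only incongruent participants can reach the rational quadrant through BBS alone.
- **Denominator.** The BBS calculation uses all 120 per arm. Adaptive shifting is possible only for those who start outside the rational quadrant.

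The risk lies in interpretation. A null result for H 2.1 would be read as coming from a test with 80% power, and the document does not establish that.

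**Working it through.** **1. Reproduce the plan's figure.** Inputs: 120 per arm, significance level 0.05 (two-sided assumed), 80% power.

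Detectable d = (1.960 + 0.842) × √(2/120) = 0.362 (0.363 with the t distribution). At d=0.36 the t-test power is 79%. The stated d=0.36 is thus the detectable standardised mean difference for two groups of 120, with no allowance for clustering.

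**2. Check the effect size against its own inputs.** 8/12 = 0.67, not 0.36. At 0.67, power with 120 per arm is 99.9%. With SD 12, d=0.36 is a difference of 0.36 × 12 = 4.3. With a difference of 8, it implies an SD of 8/0.36 = 22.2.

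**3. Power for the binary outcome.** Inputs:
- At risk per arm: the Introduction (Background) puts 64% to 79% of older adults in maladaptive FRA. As a proxy for the non-rational share, 0.64 × 120 ≈ 77 and 0.79 × 120 ≈ 95.
- PEER rate: 10%, from the sizing section.
- Control rate: the sizing section gives none. The pilot in the Discussion (Principal Findings) had none of 22. The 2% and 5% below are assumptions.
- One follow-up time point, no clustering, two-sided 0.05, exact enumeration of two independent binomials.

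*10% of those at risk shift in PEER; first figure 77 per arm, second 95 per arm:*

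| Control rate | Chi-square | Fisher exact |
|---|---|---|
| 0% (pilot) | 96%, 99% | 79%, 92% |
| 2% (assumed) | 59%, 66% | 42%, 55% |
| 5% (assumed) | 22%, 26% | 13%, 18% |

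**4. The other reading of the 10%.** The plan prints the fraction as 34/340, which has all participants as its base. On that base about 12 of 120 per arm shift, so the rate among those at risk is 12/77 = 15.6% or 12/95 = 12.6%.

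| Control rate | Chi-square (95 per arm, 77 per arm) | Fisher exact (95 per arm, 77 per arm) |
|---|---|---|
| 0% (pilot) | above 99% for both | about 98%-99% for both |
| 2% (assumed) | 85%, 91% | 78%, 83% |
| 5% (assumed) | 47%, 60% | 37%, 50% |

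**5. Clustering.** Six sites are planned, three per arm. The design effect is 1 + (m − 1) × ICC, with m = 77/3 ≈ 26 at risk per site. No site-level ICC is identified for this outcome, so 0.01 and 0.05 are assumed, giving design effects of 1.25 and 2.23. By the pooled normal approximation, power for 10% against 0% falls from 82% to 73% and 48%. Using repeated binary measures could raise power, but the documents give no correlation for them.

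**The case against.** The strongest reply is that the only control rate in the documents is the pilot's zero. At 10% against 0%, power is about 80% or more before clustering, whichever test is used. Every low figure above depends on a control rate that the documents do not give. The 10% may also be meant for all participants, which raises power further. Maladaptive FRA may not include the congruent quadrant, since the Conclusions tie it to a mismatch between body and mind; 77 to 95 at risk would then be a lower bound. A single-time-point comparison is not the planned repeated-measures model either. All of this stands, and it rules out a tempting stronger reading: a reader might infer that H 2.1 is underpowered, or that the PEER effect must be about twice the planned 10%. The documents do not support either inference.

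The pilot does not settle the matter the other way. With none of 22, the exact 95% upper limit is 1 − 0.025^(1/22) = 15%, so control rates of 2% to 5% remain compatible with it.

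It can also be said that BBS belongs to the aim 2 analysis, that the sizing section mentions a binary 10%, and that power for a secondary outcome is often left to a fuller document. The first makes a BBS calculation relevant but does not make it the power of the named H 2.1 test. The second has no comparator, test or power. The third would answer an omission, but here a power is stated and attached to FRA shifting.

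**Conclusion.** The concern holds as a mismatch. The 80% at 120 per arm belongs to a comparison of BBS means in all participants. H 2.1 is a binary test on two scales jointly, among those non-rational at T1. This conclusion does not depend on any assumed rate.

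The actual power of H 2.1 is undetermined. On the simplified calculation, chi-square power runs from 22% to above 99%, depending on the control rate (0% to 5%), the base of the 10% and the number at risk. It ignores clustering, which lowers power, and repeated measures, which may raise it.

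This is a secondary outcome and the sample size need not change. The statement should still be corrected, because readers will rely on it when they interpret H 2.1, and because d=0.36 also conflicts with the difference and SD given beside it.

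**What to change.** In Power Analysis and Sample Size:

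1. Stop describing the BBS calculation as the power for FRA shifting.
2. Reconcile d=0.36 with the difference of 8 (SD 12), then present it only as the detectable standardised difference in BBS score. Relabelling it without this step would leave a wrong figure in place.
3. Add a power or detectable-difference statement for H 2.1 as a binary outcome among participants non-rational at T1. State the expected number at risk, whether the 10% refers to them or to all participants, a range of control rates that includes the pilot's 0%, and an allowance for three sites per arm.

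The sample size is unchanged. The cost is wording and one recalculation, and the power stated for H 2.1 may be less favourable than 80%.

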### Data Analysis

We will collect demographic information from the participants for the study. We will compare baseline variables, such as essential participant characteristics, primary, and secondary end points, to summarize the differences between the 2 groups at the start of the study (T1). For the analysis of categorical data and continuous data, the chi-square test and 2-tailed *t* test will be used. We use R (version 4.1.2; R Foundation) for data analyses, with a significance level of *P*=.05.

Aim 1 is to examine the effects of the technology-based PEER intervention on fall risk, dynamic balance, and accelerometer-based PA.

The hypotheses are as follows:

*H 1.1*: The PEER group will reduce the fall risk compared with the control group.*H 1.2*: The PEER group will improve the dynamic balance compared with the control group.*H 1.3*: The PEER group will improve accelerometer-based PA compared with the control group.

Data will be analyzed according to the intention-to-treat principle [100]. We will model the fall risk, dynamic balance, and accelerometer-based PA as longitudinal outcomes consisting of 4 measurements (baseline or T1, after program completion or T2, follow-up at 3 months or T3, and follow-up at 6 months or T4) using the longitudinal linear mixed model (LMM) [101]. The LMM allows all low-income older adults and their available data to be included in the analysis, even for unequal group sample sizes, and the group heterogeneity can be addressed in the variance structure of random effects. It is hypothesized that the PEER group will show improvement in all outcome measures over time. To test hypothesis *1.1*, between-arm differences for fall risk scores, the likelihood ratio test (LRT) [101] associated with LMM will be used from all follow-up assessment visits. Similarly, the LRTs will be used to test hypotheses *1.2* and *1.3* for between-arm differences for dynamic balance and PA, respectively. The CDC-recommended scoring scheme will be adopted to process fall risk, TUG, and STS data [102]. For example, the average score of the number of STS repetitions a person can complete is based on different age and sex groups [102].

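### The planning effect sizes do not follow from their own inputs, 120 per arm cannot be reproduced from any stated primary-outcome effect, and fall risk has no power statement

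*Protocol article*

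**What the plan says.** All the planning figures stand in the protocol article, Methods, Power Analysis and Sample Size. The section names fall risk and normalized MVPA (primary) and the BBS score (secondary) as the outcomes behind the sample size.

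- Planning means for MVPA: "normalized mean MVPA between the PEER group (mean 3.67, SD 2.54) and the control group (mean 5.38, SD 2.68").
- Planning means for fall risk: "the difference in the fall risk score between the PEER group (mean 2.72, SD=3.23) and the control group (mean 2.21, SD=2.06").
- Differences to detect: "Considering a clinically relevant normalized difference in MVPA of 1.7 (SD 2.60) and a fall risk score difference of 0.50 (SD 2.56"). One Cohen d of 0.25 and one ICC of 0.8 follow, said to be used for the calculation.
- Result, which refers to MVPA measured repeatedly: "A sample size of 120 participants per arm is needed to reach 80% statistical power to detect the difference between the PEER and control groups". This sentence appears twice in succession, both times for MVPA.
- Secondary outcome: the premise is "Given the sample size of 120 per arm, a significance level of *P*=.05, and 80% power". The BBS effect is then introduced with "considering a clinically relevant BBS mean score difference of 8 (SD 12), the effect size Cohen", and its value is printed as 0.36.

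Under Aims and Hypotheses, H1.1 predicts lower fall risk with PEER and H1.3 predicts better accelerometer-based PA. Under Primary Outcome Measures, a fall risk score of 4 or more signals risk, so a higher score is worse.

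**The concern.** A standardised effect is the difference divided by its SD. The section prints both parts for three outcomes, and in no case does the printed d equal that ratio. One d also cannot stand for two outcomes whose ratios differ more than threefold.

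Two further features undermine the derivation. The differences of 1.7 and 0.50 are the gaps between the printed means (1.71 and 0.51) with the sign dropped, and as labelled those gaps run against the hypotheses. And the outcome named first as a basis for the sample size, fall risk, receives no sample size or power of its own, although it has the smallest implied effect.

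At stake is whether a reader can tell which effect 120 completers per arm would detect, and on which outcome.

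**Working it through.** **Inputs.** Differences, SDs, d = 0.25, ICC = 0.8, 80% power and 120 per arm come from Power Analysis and Sample Size. Alpha is blank in the primary sentence of the text at hand. I take .05 because the BBS sentence states it and Data Analysis repeats it ("for data analyses, with a significance level of *P*=.05"). Sidedness is not given for the sample size; I take two-sided, since Data Analysis plans that "the chi-square test and 2-tailed *t* test will be used". The section does not say what the ICC refers to; I read it as the within-person correlation r.

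**Step 1: effect sizes.**
- MVPA: 1.7/2.60 = 0.654
- Fall risk: 0.50/2.56 = 0.195
- BBS: 8/12 = 0.667
- Printed: 0.25 for the primary outcomes, 0.36 for BBS

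**Step 2: can 120 be reproduced?** By the normal approximation, n per arm = 2(1.960 + 0.842)² × V/d² = 15.70 × V/d². V is the variance factor of the design at r = 0.8:
- mean of k follow-ups: (1 + (k−1)r)/k
- change from baseline to the mean of k follow-ups: (1−r)(1 + 1/k)
- baseline-adjusted mean of k follow-ups: (1 + (k−1)r)/k − r²

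Example, fall risk at one visit: 15.70/0.1953² = 411.5, so 412; the exact t calculation gives 413. The table uses the exact two-sample t test and ignores clustering.

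| Design | V | n, MVPA (d = 0.654) | n, d = 0.25 | n, fall risk (d = 0.195) | Fall-risk power at 120 |
|---|---|---|---|---|---|
| One follow-up, baseline ignored | 1.000 | 38 | 253 | 413 | 32.5% |
| Mean of 3 follow-ups, baseline ignored | 0.867 | 33 | 219 | 358 | 36.7% |
| Change to 1 follow-up | 0.400 | 16 | 102 | 166 | 66.4% |
| Change to mean of 2 | 0.300 | 13 | 77 | 125 | 78.6% |
| Change to mean of 3 | 0.267 | 11 | 68 | 111 | 83.1% |
| Baseline-adjusted, 1 follow-up | 0.360 | 15 | 92 | 150 | 70.9% |
| Baseline-adjusted mean of 2 | 0.260 | 11 | 67 | 108 | 84.0% |
| Baseline-adjusted mean of 3 | 0.227 | 10 | 58 | 95 | 88.6% |

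No cell gives 120. The nearest are 125 and 111, both for fall risk, whereas the printed sentence concerns MVPA. If the ICC were a site-level value, 120 per arm over three sites is 40 per site, the design effect is 1 + 39 × 0.8 = 32.2, and no stated effect comes near 120.

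**Step 3: where 0.36 comes from.** With 120 per arm at one time point, the detectable effect at 80% power is d = 0.363 (0.362 by the normal approximation). In reverse, d = 0.36 needs 122 per arm (123 exact). In BBS units, 0.363 × 12 = 4.4 points. So 0.36 is an output of 120 and not the effect size of an 8-point difference.

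**Step 4: direction.**

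| Outcome | PEER | Control | PEER minus control | Hypothesis |
|---|---|---|---|---|
| Fall risk score (higher is worse) | 2.72 | 2.21 | +0.51 | PEER lower (H1.1) |
| Normalized MVPA | 3.67 | 5.38 | −1.71 | PEER better (H1.3) |

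The fall-risk reversal needs no assumption. The MVPA reversal assumes that a higher normalized value means more activity, because the normalization is not defined.

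**The case against.** **120 does match a stated effect.** The printed d of 0.36 corresponds to 120 per arm. This stands, so a reader who infers that 120 matches no stated effect at all goes too far. But 0.36 belongs to a secondary outcome and is worded as what 120 can achieve, so it is not the source of 120.

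**The model may use baseline.** Data Analysis treats T1 as one of four measurements and adds a group-by-time term, so change-type contrasts are natural. With change to the mean of two or three follow-ups, fall risk needs 125 or 111 per arm and has 79% or 83% power at 120. A reader might infer from the 33% figure that fall risk is badly underpowered; the document does not support that, because the answer turns on a model the section does not name.

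**Alpha and sidedness are open.** By the normal approximation, d = 0.25 would need 122 per arm at alpha 0.025 with a change score, or 121 at 0.0167 with one baseline-adjusted follow-up. Fall risk with one baseline-adjusted follow-up would need 117 at one-sided .05. Nothing in the text states a split or one-sided alpha, and .05 appears twice. These fits do mean that 120 should not be called impossible, only not reproducible from what is printed. They also leave d = 0.25 unequal to either ratio.

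**BBS.** A detectable effect of 0.36 below a relevant 0.67 is favourable. True: the sentence is misworded, but adequacy for BBS is not harmed before clustering.

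**Cause of the reversed means.** A reader might infer swapped labels or a baseline imbalance. The section gives no source or time point for the means, so neither can be asserted. The sign does not change a two-sided sample size.

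**The duplicated sentence** may be an editorial slip over a fall-risk sentence. That is plausible, and it does not show that no fall-risk calculation exists. Even so, d = 0.195 did not return 120 in Step 2.

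**SDs.** A reader might pool 3.23 and 2.06 to 2.71 and object to 2.56. That assumes equal arm sizes, which are not given, so it is not a discrepancy.

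**Conclusion.** The concern holds as a defect in the stated sample-size justification. The section uses d = 0.25 where its own inputs give 0.65 and 0.20, and attaches 0.36 to a BBS difference whose d is 0.67. It prints fall-risk means that contradict H1.1, and MVPA means that contradict H1.3 if higher means more activity. It repeats the MVPA sentence where a fall-risk statement would be expected.

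The size depends on the outcome. For MVPA at the stated 1.7 (SD 2.60), 120 per arm gives over 99% power before clustering. For fall risk the table's span, from about 33% to 89%, is wide enough that adequacy cannot be judged until the model is named.

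This rests on two-sided .05, 80% power, the ICC of 0.8 as within-person correlation, and no allowance for clustering. It shows that the justification cannot be checked; it does not show that the trial is too small.

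**What to change.** Rewrite the one paragraph:

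- Correct the arm labels, or replace the means with a between-arm difference in the hypothesised direction, and state their source.
- For each outcome behind the sample size (MVPA, fall risk, BBS), give one consistent set: difference, SD, resulting d, alpha and sidedness, meaning of the ICC, model, and resulting power.
- Replace the second copy of the MVPA sentence with the fall-risk figure.
- Restate the BBS line as: *about 4.4 points (d = 0.36) detectable at 80% power with 120 completers per arm, before clustering*.

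The cost is a text correction. Enrolment is unchanged; some stated figures will become less favourable, fall risk most likely among them.
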